#### Descriptive analysis

The flow of participants through each stage of the trial, including the number of individuals screened, eligible, randomised to each group, receiving allocated treatment, and included in the primary analysis will be summarised using a CONSORT flow chart (Fig. 1). Reasons for ineligibility, loss to follow-up and exclusion from the primary analysis will be summarised. Participant follow-up data will be presented by randomised group as well as COVID-19 status (pre-COVID-19/COVID-19 as in the ‘Definition of analysis populations’ section).

**Fig. 1 Fig1:**
[figure not shown]
CONSORT diagram

Baseline characteristics will be reported by the treatment group, including the minimisation factors and important prognostic, demographic and clinical covariates. Numbers (with percentages) for binary and categorical variables and means (and standard deviations), or medians (with lower and upper quartiles) for continuous variables will be presented, there will be no tests of statistical significance nor confidence intervals for differences between randomised groups on any baseline variable. Baseline characteristics will also be reported by COVID-19 status in order to explore the difference in demographics between these groups.

It is likely that some data may not be available due to voluntary withdrawal of participants, lack of completion of individual data items or general loss to follow-up. The number (with percentage) of withdrawals from the trial and the numbers lost to follow-up for the primary outcome together with the associated reasons (where possible) will be reported by the treatment group. Any deaths (and their causes) will be reported separately.

#### Analysis of the primary outcome

The primary outcome measure, the role of usual care versus usual care plus the experimental intervention upon the UCLA Activity Score at 12 months post-randomisation, will be modelled using a mixed effects model. This model will account for person within centre random effects, and Charlson Comorbidity Index score and baseline UCLA Activity Score (as continuous outcomes), type of operation the patient is undergoing (THR or TKR), time (6 or 12 months) and treatment as fixed effects. Treatment by time point interactions will also be included in the model to allow time-specific treatment effects to be calculated. This model uses all available data at each time point. Comparison will be performed on an intention-to-treat basis and results presented as comparative summary statistics (i.e. difference in means) with 95% confidence intervals.

The appropriateness of the assumption of approximate normality of the residuals of this model will be assessed graphically. If the residuals are not normally distributed, the outcome data will be log-transformed to gain normality and geometric means with 95% confidence intervals will be reported. If data is not normally distributed after log-transformation, the non-parametric Mann-Whitney test will be used with no adjustment for baseline or stratification factors, and the difference in medians with 95% confidence intervals will be reported.

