### Outcomes

#### Primary outcome

The primary outcome measure is the UCLA Activity Score 12 months post-randomisation. The UCLA Scale is a reliable and valid self-reported tool to assess physical activity [17, 18] that assesses global activity levels with a grading system of 1 to 10 where 1 equates to “wholly inactive, dependant on others and cannot leave residence” and 10 refers to “regularly participates in impact sports”.

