
### Sample size

Two hundred fifty participants (125 per arm) are required to detect a standardised effect size of 0.4 with 80% power and 5% (2-sided) significance, allowing for 20% loss to follow-up. These calculations are based on the primary outcome at 12 months post-randomisation, assuming a baseline standard deviation of 2.5 [17] and a between-group difference of one. Our target standardised effect size is derived from the UCLA Activity Score’s minimal clinically important difference of 0.92 [17]. The sample size was increased to 260 to account for the change in allocation ratio, maintaining the same power and type I error rate.

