##### Missing data

Missing data analysis will be performed on the primary outcome only. The primary analysis multi-level model using repeated measures is relatively robust to missing data under the missing at random (MAR) assumption [30].

Analysis will be performed on an intention-to-treat basis. The number and percentage of participants in the missing category will be presented, as well as reasons for missingness if known. Missing data will be reported and summarised by the treatment group. The distribution of missing data will be explored to assess the assumption of data being missing at random under which the principal analyses will be conducted. Varying scores of the UCLA Activity Score (e.g. 30th, 40th, 50th, 60th, 70th quantiles) will be imputed where data is missing and these ‘complete’ datasets will be reanalysed, using the same model used in the primary analysis and the results presented in graphical form. This analysis will be undertaken if there is more than 5% missing data for the primary outcome at 12 months.

If there is evidence that there is a departure from the MAR assumption, a search for factors not included in the primary analysis model that explains missingness will be performed and if variables are found, multiple-imputation using chained equations [31] will be utilised, using the primary analysis model but including these variables to assess the sensitivity of the findings to missing data. If no variables are identified, multiple-imputation will not be performed.

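### A graphical residual check can replace the primary adjusted mean difference with geometric means, then with an unadjusted Mann-Whitney test, so the primary estimand depends on the data

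*SAP article*

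**What the plan says.** Under 'Analysis of the primary outcome', the SAP article specifies a mixed model for the UCLA Activity Score at 6 and 12 months. It has person within centre as random effects, and baseline score, Charlson index, operation type, time, treatment and treatment by time as fixed effects. The result is a difference in means with a 95% confidence interval.

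The same section then makes this conditional on a graphical check that the residuals are approximately normal. If they are not, "the outcome data will be log-transformed to gain normality and geometric means with 95% confidence intervals will be reported". The next step is: "If data is not normally distributed after log-transformation, the non-parametric Mann-Whitney test will be used with no adjustment for baseline or stratification factors", with a difference in medians as the estimate. The section does not say that the mixed model remains primary after either step.

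Three other sections bear on this:

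- 'Primary outcome': the scale "assesses global activity levels with a grading system of 1 to 10".
- 'Sample size': the target was set "assuming a baseline standard deviation of 2.5 [17] and a between-group difference of one", and derived from a "minimal clinically important difference of 0.92".
- 'Missing data': "The primary analysis multi-level model using repeated measures is relatively robust to missing data under the missing at random (MAR) assumption".

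**The concern.** The trial has one primary outcome and one final analysis. Which quantity that analysis estimates, what it adjusts for and how it treats missing scores are all left to a look at residual plots from the final data. Three different effect measures are possible: a difference in means, a contrast of geometric means, and a difference in medians. Only the first is on the scale on which the trial was sized and on which the MCID is stated.

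The last step has two further costs. A two-sample rank test at 12 months uses only the observed 12-month scores, so the model on which the plan rests its missing-data argument is no longer the primary analysis. The p-value and the estimate also come apart. Mann-Whitney compares whole distributions and does not test a difference in medians, so the two can disagree.

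**Working it through.** **Inputs from the SAP article.** Difference 1.0, SD 2.5, 80% power, 5% two-sided, 20% loss ('Sample size'). Allocation 1:1 for 75 participants, then 2:1 ('Trial design'). 230 randomised ('Trial status'). Score graded 1 to 10 ('Primary outcome').

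**Assumption.** The correlation ρ between baseline and 12-month score is not given, so a range of 0 to 0.7 is shown.

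**1. The plan's own figure.** Per arm, n = 2(1.96 + 0.842)² / 0.4² ≈ 98.1, so 99. Then 99/0.8 = 123.75, so 124 per arm and 248 in total, against the stated 250. At 260, usual care has 37.5 + 185/3 ≈ 99 and the intervention arm about 161. After 20% loss, power is 80.0%. Both stated sizes reproduce, and both are for an unadjusted difference in means.

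**2. Power under the plan's normal model, 230 randomised.** Usual care: 37.5 + 155/3 ≈ 89.2. Intervention: ≈ 140.8. After 20% loss: 71.3 and 112.7, about 184 in all.

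- Unadjusted: SE = 2.5 × √(1/71.3 + 1/112.7) ≈ 0.378.
- Baseline-adjusted (a simple stand-in for the mixed model): SE × √(1 − ρ²).
- Mann-Whitney: SE / √0.955, where 0.955 is its asymptotic relative efficiency under normality.
- Power = Φ(1/SE − 1.96).

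| Assumed ρ | Adjusted | Mann-Whitney | Relative efficiency, 0.955(1 − ρ²) |
|---|---|---|---|
| 0 | 75.3% | 73.4% | 0.955 |
| 0.3 | 79.1% | 73.4% | 0.869 |
| 0.5 | 86.3% | 73.4% | 0.716 |
| 0.7 | 95.9% | 73.4% | 0.487 |

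**3. Power when the data are not normal.** These are simulated scores, rounded and limited to 1 to 10, with a 1-point shift, 230 randomised, 20% random loss and 3,000 replicates.

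| Shape | ρ | Adjusted | Mann-Whitney |
|---|---|---|---|
| Right-skewed | 0.3 | 84.5% | 90.4% |
| Right-skewed | 0.5 | 88.6% | 90.5% |
| Right-skewed | 0.7 | 96.8% | 89.3% |
| Heavy-tailed | 0.3 | 91.3% | 93.6% |
| Heavy-tailed | 0.5 | 95.2% | 93.3% |
| Heavy-tailed | 0.7 | 99.2% | 93.6% |

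The loss of power is therefore conditional. It grows with ρ, and at lower ρ it can reverse for the kind of data that would trigger the switch.

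**4. The median difference on this scale.** Medians of integer scores move in steps of 0.5 or 1. With a near-normal latent score (mean 5 assumed, SD 2.5) and a latent 1-point shift, the sample median difference was exactly 0 in about 10% of trials, 1 in about 73% and 2 in about 10%.

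**5. Missing data, no true effect.** Dropout was made to depend on baseline in opposite directions in the two arms, a deliberately strong pattern. The baseline-adjusted analysis rejected in 5.2/4.8/5.8% of trials at ρ = 0.3/0.5/0.7. Unadjusted Mann-Whitney rejected in 10.6/20.8/34.6%. With dropout completely at random and ρ = 0.5, both rejected in 4.9%. This shows what is lost if missingness depends on baseline. It does not predict what will happen in this trial.

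**The case against.** The cascade is written down and ordered in advance, and the Discussion commits to justifying deviations. It asks only for approximate normality, and Mann-Whitney is reached only after two failures. With a near-normal integer score (SD 2.5, ρ = 0.5), simulated residuals had mean absolute skewness of about 0.11 to 0.16 and excess kurtosis of about −0.4, which a plot could well pass. The article is a condensed account, so the lack of a numerical threshold deserves little weight. 'Supporting analyses of the primary analysis' also plans two further mixed models, not tied to the residual check, so adjusted repeated-measures estimates would still appear.

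Most of this stands, but it concerns how likely the switch is. It does not change what the switch does. A pre-specified rule that selects among three estimands still leaves the primary estimand to the data. The supporting mixed models would then be supporting an analysis of a different kind.

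A reader might infer four stronger things that the documents do not support:

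- *A ten-grade score makes the switch certain.* The criterion is approximate normality.
- *The rank test is always less powerful.* The skewed and heavy-tailed results show otherwise.
- *Its estimate can hardly resolve an effect near the MCID.* With a 0.5-point shift, about half the MCID, the median difference is exactly 0 in about 45% of trials. With a 1-point shift it is 0 or below in about 12% at an assumed mean of 5, and in roughly a quarter at 4.5 or 5.5. That is coarse, but not uninformative.
- *The switch removes all protection against the change in allocation ratio.* The primary model has no term for allocation phase or calendar period, so at most indirect covariate adjustment is lost.

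**Conclusion.** The point holds in this form. The plan lets a residual plot take the primary result off the raw-point mean difference on which the sample size and the MCID of 0.92 rest. Its final step discards the baseline score, Charlson index, operation type, centre and 6-month data, so the missing-at-random argument no longer covers the primary result. It also pairs a p-value with an estimate which that p-value does not test. These consequences follow from the text and need no assumption about the data.

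The size of the power loss does need assumptions. Under normality with SD 2.5, 230 randomised and 20% loss, it is about 2, 6, 13 and 22 percentage points at ρ = 0, 0.3, 0.5 and 0.7. The claim is only that power falls when baseline is prognostic. With about 184 participants expected at 12 months, an interval for a mean difference does not need normal residuals, so the switch solves little.

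**What to change.** In 'Analysis of the primary outcome':

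- Delete the log-transformation and Mann-Whitney replacement steps.
- State that the adjusted mixed-model difference in means at 12 months is the primary analysis whatever the residual plots show.
- Pre-specify one sensitivity analysis, to be reported regardless of the plots: a robust or a bootstrap confidence interval for the same mean difference. Choose which now, and for a bootstrap state the resampling unit, since the model includes centre and there are eight centres. Making this conditional on the plots would bring back the same problem.
- Label any ordinal, rank or log-scale analysis as sensitivity only, preferably with the primary model's covariates.

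The cost is a wording change and a small amount of extra analysis. The article places data lock after its writing, so the change could be made before results are seen.

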#### Supporting analyses of the primary analysis

An area under the curve (AUC) analysis will be performed for the UCLA Activity Score. Estimates will come from the same mixed model used in the analysis of the primary outcome except including baseline UCLA Activity Score in the ‘time’ fixed effect allowing time point-specific treatment effects to be calculated for baseline, six months and 12 months. These estimates will be used to calculate the AUC. Using the estimates from the mixed-effects model rather than raw, unadjusted estimates results in less bias estimates of the AUC when missing data are present [29].

Complier average causal effect (CACE) analyses will be performed to find estimates for the causal effect of actually receiving the treatment and the overall treatment effect (including non-compliers) through intention to treat analysis. The definitions of Strict Compliance, Compliance and Attendance will be used to perform three CACE analyses.

A supporting analysis of the primary outcome will use a three-level model with participants within predominant treating physiotherapist within the centre to examine the potential physiotherapist (random) effects. This model will formally incorporate terms that allow for possible heterogeneity in responses for participants due to the recruiting centre and the physiotherapist. The model will include the same fixed effects used in the primary analysis model as well as treatment by time point interactions.

An additional supporting analysis of the primary outcome using a reduced version of the primary analysis model, only using a person as a random effect, will be performed. This model is pertinent as Usual Care should be homogenous across the recruiting centres in a pragmatic trial so using a simpler model may yield a better-fit model. Model fit compared to the primary analysis model will be assessed using information criteria.

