## Methods

### Trial design

The trial is an open, phase III, pragmatic, parallel, two-arm, two-way superiority randomised controlled trial (RCT) on individuals investigating the effectiveness of usual care plus a group exercise and behaviour-change intervention versus usual care alone to increase physical activity following primary THR or TKR. Neither participants nor physiotherapists can be blinded to the treatment allocation. Primary comparison is assessed at 12 months post-randomisation with data being collected at baseline (pre-operatively), 6 months and 12 months post-randomisation.

Participants will be screened for inclusion in the trial pre-operatively, consented pre-operatively and eligibility confirmed post-operatively. They will then be randomised prior to hospital discharge and notified of their group allocation to facilitate the organisation of their rehabilitation. Initially, participants were randomised to the two groups 1:1 using minimisation by trial centre, type of joint replacement (THR or TKR), and Charlson co-morbidity index (1–3 or ≥4). The minimisation algorithm will have a probabilistic element of 0.8 included to ensure unpredictability of treatment assignment.

After 75 randomisations, the random allocation ratio was changed to 2:1 (Experimental Intervention: Usual Care). This change was made to ensure more participants were randomised to the experimental intervention group. The intervention is group-based and is designed to have three or more participants per group session. Based on evidence from early recruiting sites, there was difficulty to consistently fill sessions under a 1:1 allocation ratio. Therefore this change was deemed important to facilitate larger groups. This change was implemented by the Trial Management Group and approved by the Data Safety Monitoring Committee, Sponsor and Research Ethics Committee.

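### The supporting AUC analysis estimates a treatment effect at a pre-randomisation baseline and carries it into the AUC: unbiased, but needlessly imprecise and sensitive to chance baseline imbalance

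*SAP article*

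**What the plan says.** In the SAP article, 'Analysis of the primary outcome', baseline UCLA is a covariate and only the two follow-up visits are outcomes: the model lists "baseline UCLA Activity Score (as continuous outcomes), type of operation the patient is undergoing (THR or TKR), time (6 or 12 months"). It adds an interaction: "Treatment by time point interactions will also be included in the model to allow time-specific treatment effects to be calculated".

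Under 'Supporting analyses of the primary analysis' the AUC model changes the role of baseline: "Estimates will come from the same mixed model used in the analysis of the primary outcome except including baseline UCLA Activity Score in the" set of visits that make up the time factor. The purpose given for this change is "allowing time point-specific treatment effects to be calculated for baseline, six months and 12 months". How the AUC is then obtained is put in one sentence: "These estimates will be used to calculate the AUC".

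The order of events is under 'Trial design', with "data being collected at baseline (pre-operatively), 6 months and 12 months post-randomisation". After surgery and confirmation of eligibility, "They will then be randomised prior to hospital discharge". Allocation was made "using minimisation by trial centre, type of joint replacement (THR or TKR), and Charlson co-morbidity index (1–3 or ≥4"), so baseline UCLA was not a balancing factor.

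**The concern.** Baseline UCLA is recorded before allocation, so any difference between the arms at baseline is chance. The AUC model nevertheless gives that difference its own treatment term and passes it to the AUC. No section sets the term to zero, subtracts it or adjusts for it.

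It enters by two routes. The baseline estimate has a direct weight in the AUC. In addition, because baseline is now an outcome with a free treatment-by-time term, the 6- and 12-month contrasts are no longer adjusted for it.

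What is at stake is the usefulness of a supporting analysis. Its interval is wider than the data require. It may also differ from the primary result, or agree with it, partly because of an imbalance that the primary model removes.

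**Working it through.** **The plan's own figure.** The plan states no figure for the AUC analysis. Its sample size supplies the SD and can be reproduced. A difference of 1 with SD 2.5, 80% power and two-sided 5% needs 99 per arm by the normal formula, or 100 by the t distribution. Dividing by 0.8 for 20% loss gives 248 or 250 in total, against the stated 250.

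**Inputs from the SAP article**
- SD 2.5, given for baseline ('Sample size').
- 230 randomised ('Trial status'), with 1:1 allocation for 75 and then 2:1 ('Trial design'). Expected arms: 37.5 + 155 × 2/3 = 140.8 and 37.5 + 155/3 = 89.2.

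**Assumptions not in the plan**
- SD 2.5 at every visit and complete data.
- Trapezoid total AUC over 0, 6 and 12 months, divided by 12. The weights are then 1/4, 1/2 and 1/4.
- Correlation a between baseline and each follow-up, and b between 6 and 12 months.

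**Standard error of the baseline difference:** 2.5 × √(1/140.8 + 1/89.2) = 0.338.

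**Variance of the averaged AUC difference, in units of 0.338²**
- As planned: 0.375 + 0.375a + 0.25b.
- Baseline effect fixed at zero (follow-up contrasts conditional on baseline): 0.3125(1 − a²) + 0.25(b − a²).
- Planned minus fixed: (0.25 + 0.75a)².

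The factor 0.25 + 0.75a is also the amount by which the planned AUC difference moves per point of baseline imbalance. The shift and the loss of precision are therefore the same quantity.

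| a, b | Variance, plan | Variance, fixed | SE, plan | SE, fixed | SE increase | Shift for a one-SE imbalance |
|---|---|---|---|---|---|---|
| 0.3, 0.6 | 0.6375 | 0.4119 | 0.270 | 0.217 | 24% | 0.16 |
| 0.3, 0.3 | 0.5625 | 0.3369 | 0.254 | 0.196 | 29% | 0.16 |
| 0.5, 0.5 | 0.6875 | 0.2969 | 0.281 | 0.184 | 52% | 0.21 |
| 0.7, 0.7 | 0.8125 | 0.2119 | 0.305 | 0.156 | 96% | 0.26 |

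SEs and shifts are in UCLA points of averaged AUC. With all correlations zero the variances are 0.375 and 0.3125, a ratio of 1.20 (SE about 10% larger), because the baseline noise is still added directly.

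**Scale.** A true difference of 1 point at both follow-ups gives an averaged AUC difference of 0.5 + 0.25 = 0.75.

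**If the AUC is taken above baseline.** The weights become −0.75, 0.5 and 0.25. At a = b = 0.5 the planned variance is 0.875 − 0.4375 = 0.4375 against 0.2969, so the SE is √(0.4375/0.2969) = 1.21 times as large. The shift per point of imbalance changes sign: −0.75 + 0.75 × 0.5 = −0.375.

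**Simulation check.** In 20,000 trials with 141 and 89 participants, all correlations 0.5 and true effects 0, 1 and 1, both estimators averaged 0.75. Their SDs were 0.281 (plan) and 0.184 (fixed). The slope on the baseline difference was 0.62 for the plan and −0.002 for the fixed version.

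**The case against.** The strongest reply is that nothing here is invalid. The planned estimator is unbiased over randomisation, and a correctly computed interval already contains the variation due to baseline imbalance. A reader might infer that chance imbalance biases the AUC result or spoils its coverage. The plan does not support that, and the simulation means agree. Nor are the shift and the wider interval two separate harms: at correlation 0.5, √(0.281² − 0.184²) = 0.21, which is the shift itself. This reply stands.

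The size is also open to challenge. The plan gives one SD, for baseline, and no correlations. Surgery lies between baseline and both follow-ups, so equal correlation across all visits is not a safe default, and a weaker link to baseline brings the penalty down to about 24%. The AUC formula is not stated either. This stands too, and is why a range is shown. In every case examined, though, the penalty is above zero.

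Third, this is one of several supporting analyses. The primary 12-month comparison keeps baseline as a covariate, and baseline characteristics are tabulated by arm, so a discrepancy due to imbalance could be recognised. That limits the importance of the point but is no reason to keep the weaker analysis.

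Not all adjustment is lost. The Charlson index and operation type stay in the model, and baseline still informs participants with missing follow-up, which is the stated reason for using model estimates. The fix keeps that benefit. If baseline were meant to stay as a covariate as well, it would be both outcome and predictor in one model, and the text would still need correcting.

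**Conclusion.** The point holds as one of efficiency and robustness in a supporting analysis. A treatment effect known to be zero is estimated and used. The AUC contrast is therefore less precise than it need be and, in the realised trial, moves with an imbalance that the primary model adjusts for.

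Under the assumptions in the working, the SE is about 24% to 96% larger for total AUC over the correlations shown, and about 21% larger for AUC above baseline at 0.5. The 52% figure belongs to a single common correlation of 0.5 and should not be read as the plan's actual loss. A one-SE baseline imbalance of 0.34 points moves the averaged total AUC difference by 0.16 to 0.26 points, which is the same loss seen conditionally.

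A reader might go further and infer that the trial's main conclusion is at risk. The documents do not support this: the primary model has baseline as a covariate, and the AUC result carries no confirmatory claim.

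**What to change.** State that the AUC model keeps baseline as a level of time but has no treatment term at baseline, so that both arms share one baseline mean. Form the AUC contrast from the 6- and 12-month effects and take its standard error from their joint covariance. State the AUC formula as well. This keeps the plan's missing-data aim and costs a sentence or two. Follow-up was still under way according to 'Trial status', and the 'Discussion' section already provides for changes to be described and justified.

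Alternatively, keep baseline as a covariate, as in the primary model, and report 6 × d6 + 3 × d12 point-months, where d6 and d12 are the adjusted effects at 6 and 12 months. This has a small cost: participants with missing baseline UCLA drop out unless it is imputed. The result is also only a linear combination of the two effects that the primary model already gives.
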